### Safety

2.10

The pre-defined safety outcomes of this study are the incidence rates of adverse events (AEs) and serious adverse events (SAEs). A serious adverse event (SAE) was defined as any untoward medical occurrence during trial participation that results in death, is life-threatening, requires hospitalization or prolongation of existing hospitalization, or results in persistent or significant disability/incapacity. This includes, but is not limited to, the emergence or clinically significant exacerbation of suicidal or severe self-injurious ideation or behavior during the intervention. A non-serious adverse event is defined as any unfavorable medical occurrence in a participant, regardless of its causal relationship to the intervention.

Researchers will closely monitor participants’ emotional state and safety behaviors throughout the trial. All AEs will be documented in detail on an adverse event form, recording their nature, severity, time of onset, duration, actions taken, and potential relationship to the intervention. In the event of any SAE, the research team will report it to the Principal Investigator and the Ethics Committee within 24 hours. The affected participant will be withdrawn from the study immediately and will receive necessary medical care. The sponsor will provide compensation for any harm directly caused by the trial intervention, in accordance with relevant regulations.

To minimize risks, a corresponding contingency plan will be established prior to the study commencement, and the following measures will be implemented: ensuring a safe environment for activity sessions, guaranteeing the presence of at least one healthcare professional on-site, and equipping the site with a complete first-aid kit and basic emergency equipment. Only safety-designed tools (e.g., rounded shovels, plastic scissors) are permitted. Participants will receive instruction on the proper use and safety precautions of the tools before activities begin. Individuals with a known history of allergy to pollen, soil, or related materials will be excluded during the screening phase. Should any signs of an allergic reaction occur during an activity, the contingency plan will be activated immediately and managed by the on-site healthcare professional.

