#### Discontinuation criteria

2.2.3

Participants may be withdrawn or discontinued from the study if any of the following criteria are met: (1) Poor adherence or failure to complete study-specified assessments; (2) Incomplete medical records affecting the evaluation of primary or secondary outcomes; (3) Voluntary withdrawal of informed consent by the participant or their legal guardian; (4) Experiencing significant clinical deterioration, serious complications, or special physiological changes during the study that make continued participation unsuitable; (5) The investigator determines, for other justified reasons, that continued participation is not appropriate.

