#### Treatment as usual

2.4.1

This study aims to evaluate whether adding TH to a standardized regimen of treatment as usual (TAU) provides additional benefit. To independently assess the additive effect of TH as an adjunctive therapy, the control group receives two weeks of TAU during the trial period. All TAU is provided according to the hospital’s standard clinical pathways. TAU comprises treatment and usual care. The treatment consists of antidepressant medication, supplemented by physical therapy, psychotherapy, and rehabilitation training. The usual care includes admission orientation, health education on symptoms, consequences and treatment options for depression and NSSI as well as the importance of treatment adherence, medication guidance, discharge planning, and psychological support.

During the study period, the provision of TAU is at the discretion of the attending physician. Participants are not restricted from receiving other treatments or care beyond the designated protocol. To address potential heterogeneity in TAU, the following TAU components will be systematically recorded for all participants throughout the trial: antidepressant medication, including drug name, daily dose, and any dose adjustments; physical therapy, including type, frequency, and duration; psychotherapy, including modality, number of sessions, and duration; and rehabilitation training, including type and frequency. If a participant’s symptoms worsen and require additional treatment, all related details are fully documented in the case report form. These data will be incorporated into the statistical analysis to control for potential confounding effects.

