### Data collection and quality control

2.6

At the baseline assessment(T_0_), the researcher will collect participants demographic data (age, gender, residence, only-child status, family structure, and family economic status, etc.) and Disease-related information (age of onset, duration of illness, and family history of mental illness, etc.). All outcome measures (primary and secondary outcomes) will be assessed at both baseline (T_0_) and immediately post-intervention (T_1_). These measures comprise the ASHS, HAMD-17, TAS-20, GSES, PSQI, and UCLA-LS.

The following quality control measures will be implemented to ensure standardization and accuracy in data collection and entry:

All researchers will receive systematic training to ensure the standardization and consistency of scale administration and data collection.Assessments for each participant at all study time points will be conducted by the same researcher member whenever possible.This trial employs well-established scales and questionnaires with good reliability and validity.Researchers will administer the scales and questionnaires to participants in a quiet, indoor setting using a one-on-one format. Standardized instructions will be provided to explain the scales and questionnaires, ensuring participants correctly and fully understand the items. Upon completion, the scales and questionnaires will be collected immediately. Researchers will then check for completeness. Any missing items will be clarified with the participant and promptly completed.After collection, all scales and questionnaires will undergo initial screening and coding. Data will then be entered into an electronic database using a double-data entry method by two independent personnel. Any discrepancies between the two entries will be adjudicated by a third researcher through verification against the original paper records.

For participants who discontinue the intervention early, every effort will be made to collect all primary and secondary outcome measures at the originally scheduled time point, T_1_. If a participant withdraws consent for further participation but agrees to data use, data collected up to the point of withdrawal will be retained and included in the ITT analysis. Reasons for discontinuation will be documented. In the ITT analysis, missing outcome data from early withdrawals will be handled using multiple imputation as the primary method, with the last observation carried forward used in sensitivity analyses.

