### Statistical methods

2.9

Statistical analysis will be conducted by an independent statistician blinded to group allocation using SPSS 26.0 software. The analysis will adhere to the intention-to-treat (ITT) principle, employ two-sided tests, and consider a P-value of less than 0.05 as statistically significant.

The analysis of outcome measures will utilize three datasets: the full analysis set (FAS), the per-protocol set (PPS), and the safety set (SS). The FAS includes all randomized participants, analyzed according to their originally assigned groups. This is the primary dataset for efficacy analysis. All randomized participants are analyzed in the groups to which they were initially allocated. For missing data in the FAS, the primary outcome will be handled using multiple imputation to generate a complete dataset, upon which the primary analysis will be based. To assess the robustness of the results, a sensitivity analysis will be performed using the last observation carried forward (LOCF) method for imputation. The PPS includes participants with good adherence, who completed the full intervention, and had no major protocol deviations. This set will serve as another sensitivity analysis dataset to verify the stability of the primary analysis results. The SS includes all participants who received at least one dose of the intervention and is used for safety analyses. The evaluation of intervention effects for primary and secondary outcomes will primarily draw conclusions based on the analysis of the multiply-imputed FAS. The results from the LOCF-imputed FAS analysis and the PPS analysis will serve as sensitivity analyses to support the robustness of the conclusions. Safety indicators, such as the incidence of allergic reactions and adverse events, will be analyzed within the SS.

This study will conduct sensitivity analyses to evaluate the robustness of the results. These analyses will include repeating the primary analysis based on the FAS with missing data imputed using the LOCF method, as well as repeating the primary analysis on the PPS. If any baseline variables show imbalance (*P* < 0.1), they will be included as additional covariates in the model, followed by a corresponding sensitivity analysis.

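### Any serious adverse event, including worsening self-injury, removes the participant from the study, so the only post-randomisation NSSI score can be lost because it worsened

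*Protocol article*

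**What the plan says.** The primary outcome is the change in NSSI level score on the ASHS from T0 to T1 (section 2.5.1). Table 1 and section 2.6 schedule the ASHS at those two times only.

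Four places govern what follows when a participant gets worse:

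- **Section 2.10 (Safety)** includes in its SAE definition "the emergence or clinically significant exacerbation of suicidal or severe self-injurious ideation or behavior during the intervention". After any SAE: "The affected participant will be withdrawn from the study immediately and will receive necessary medical care". There is no condition on causality and no mention of later assessment.
- **Section 2.2.3, criterion (4)** permits, but does not require, withdrawal from the study on "Experiencing significant clinical deterioration, serious complications, or special physiological changes during the study that make continued participation unsuitable".
- **Section 2.6** says: "For participants who discontinue the intervention early, every effort will be made to collect all primary and secondary outcome measures", at the planned T1. It then says that "missing outcome data from early withdrawals will be handled using multiple imputation as the primary method", with last observation carried forward (LOCF) as a sensitivity analysis.
- **Section 2.4.1** provides that if a participant's "symptoms worsen and require additional treatment, all related details are fully documented in the case report form", which implies that some who worsen remain in the trial.

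Section 2.9 sets the primary analysis population: "The FAS includes all randomized participants, analyzed according to their originally assigned groups". A further sensitivity set is narrower: "The PPS includes participants with good adherence, who completed the full intervention, and had no major protocol deviations".

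**The concern.** One trigger for compulsory withdrawal overlaps the quantity the trial measures. If section 2.10 is followed literally, a randomised participant whose self-injury worsens badly leaves before T1 and enters the full analysis set with an imputed score. No intermediate visit exists to inform that imputation. Standard multiple imputation assumes that, given the observed data, missingness does not depend on the unseen score. Here it would depend on it directly.

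The planned sensitivity analyses do not recover the lost score. LOCF inserts the baseline value from before the worsening. The per-protocol set drops TH participants who did not finish.

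At stake is a bias in the primary contrast whose size and direction depend on how many such losses fall in each arm, and a departure from the intention-to-treat principle that section 2.9 adopts.

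**Working it through.** **1. The rules side by side.** Take a TH participant with an SAE of worsening self-injury in week 1. Section 2.10 says they leave the study. Section 2.6 says T1 is sought, because they have stopped the intervention. Neither says which prevails. Now take a control with the same event. Section 2.10 again removes them from the study. Section 2.6 hardly applies, since they have no TH to stop and their usual care continues.

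**2. The plan's own figures (section 2.8).** Difference 13, SD 17.59, two-sided α 0.05, power 80%.

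- n = 2 × (1.960 + 0.842)² × 17.59² / 13² = 28.74, rounded up to 29 per arm.
- 29 / 0.90 = 32.2, rounded up to 33 per arm, 66 in total. This reproduces.

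**3. Simple bound.** Suppose k of 33 in one arm lose T1, and their true scores exceed the imputed values by e SDs. That arm's mean is understated by (k/33) × e × 17.59. For e from 0.5 to 2:

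| k | Points | % of 13 |
|---|---|---|
| 1 | 0.27–1.07 | 2–8 |
| 2 | 0.53–2.13 | 4–16 |
| 3 | 0.80–3.20 | 6–25 |

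**4. Simulation.** Assumptions: 33 per arm, T0 and T1 bivariate normal with SD 17.59, correlation r = 0.5 unless stated, true difference 13, ANCOVA on T0. Multiple imputation from T0 and arm is approximated by ANCOVA on retained participants, which has the same expected estimate. There were 4,000 trials per setting (8,000 for the threshold settings). The yardstick is SE = 17.59 × √(1 − 0.5²) × √(2/33) = 3.75.

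| T1 losses | Shift in points |
|---|---|
| Worst 1, 2 or 3 worseners, one arm only | 0.87, 1.63, 2.34 |
| Same, r = 0.3 (k = 1 to 3) | 0.90 to 2.78 |
| Same, r = 0.7 (k = 1 to 3) | 0.60 to 2.03 |
| 1, 2 or 3 at random from one arm's worst 8 | 0.52, 1.07, 1.68 |
| TH 2 vs control 1 | 0.76 |
| TH 3 vs control 2 | 0.72 |
| 3 vs 3 | 0.00 |

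The r = 0.3 and r = 0.7 ranges cover selection on change or on the T1 score. In the first row, 0.87/13 = 7% and 2.34/13 = 18%; against the SE, 0.87/3.75 = 0.23 and 2.34/3.75 = 0.62.

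**5. One threshold for both arms.** Assume withdrawal when the score worsens by more than 25 points and TAU patients do not change on average. At r = 0.5 the SD of change is 17.59 × √(2 × 0.5) = 17.59.

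- Control: 25/17.59 = 1.42, upper tail about 0.078, × 33 ≈ 2.6 lost.
- TH with a true effect of 13: 38/17.59 = 2.16, upper tail about 0.015, × 33 ≈ 0.5 lost.
- Simulated losses are 2.55 and 0.50, and the shift is 1.61 **against** TH.
- With no true effect, about 2.5 are lost per arm and the shift is −0.02.
- If TAU patients improve by 10 and the true effect is 13, losses are 0.78 control and 0.11 TH, and the shift is 0.62 against TH.

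**6. Would LOCF expose it?** Remaining shift under LOCF for TH losses of 1, 2 and 3:

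| Mean TAU improvement | Shift |
|---|---|
| 0 | 0.71, 1.22, 1.56 |
| 10 | 0.41, 0.59, 0.66 |
| 15 | 0.25, 0.29, 0.19 |

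With 3 lost in each arm, LOCF moves by −1.17 (about 13 × 3/33) although imputation is unbiased. A gap between the two analyses is therefore only a partial signal.

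**The case against.** The strongest reply is that section 2.10 describes clinical action and section 2.6 the data rule. Section 2.6 makes no exception for SAEs and treats withdrawal of consent as the separate case in which data stop. Section 2.10 never says that T1 is not collected. On that reading the fault is loose wording, and actual loss of T1 is an inference. This reading is possible for TH participants. It does not remove the word *study* from section 2.10, and it does little for controls.

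Several further points stand in whole or in part:

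- Section 2.4.1 is weak support for the concern. Ordinary worsening and an SAE are different thresholds, so both rules can be followed together.
- Criterion (4) of section 2.2.3 is discretionary and limited to cases where continuing is unsuitable.
- The overlap with the primary outcome is partial. An SAE may be suicidal ideation or a medical event in someone whose NSSI score is not among the worst.
- The imputation model is not given in the article. If it uses the recorded TAU data, the shifts would be somewhat smaller.
- SAEs are reported as safety outcomes and reasons for stopping are documented, so the harm is not hidden.

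None of this removes the core point, which needs only sections 2.10 and 2.6 and the single post-baseline visit.

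**Conclusion.** The concern holds and should be fixed. As written, section 2.10 can leave a randomised participant without the primary outcome because that outcome worsened, and section 2.6 does not resolve the conflict for both arms.

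The likely bias is modest and its direction is not fixed by the document. One-arm loss of the worst 1 to 3 is an upper case, at 0.2 to 0.6 of a standard error. Slightly unequal losses cost about 6% of the planned difference, and equal losses cost nothing. With one rule applied evenly and a TH that works, the effect is understated. Bias in favour of TH would need more SAEs, or stricter use of the rule, in the TH arm.

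The loss counts, the 25-point threshold, the correlations and the normal model are all assumptions, so the magnitudes are illustrative. The reading of the text does not depend on them.

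**What to change.** - **Section 2.10:** state that an SAE may stop TH, as the treating clinicians decide, but does not end study participation.
- **Section 2.2.3, criterion (4):** make the same distinction for clinical deterioration.
- **Section 2.6:** extend the commitment so that the T1 ASHS is sought at the scheduled time, when clinically safe, for every randomised participant in both arms unless consent is withdrawn.

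The cost is two or three sentences and a minor amendment. Outcome assessment already takes place on the same closed ward (section 2.2.1), so little extra work follows. Some T1 scores will come from participants who stopped TH, which is what intention to treat calls for. A few medically unstable patients may still be impossible to assess. The change is worth making promptly, because no analysis can recover a T1 score that was never collected.

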## Discussion

3

Current evidence indicates that TH can effectively alleviate stress and mental fatigue in adolescents stemming from academic, interpersonal, or treatment-related pressures (41), demonstrating significant potential for improving adolescent mental health. However, clinical evidence supporting the efficacy of TH specifically for adolescents with MDD and comorbid NSSI remains scarce. Therefore, this study is designed as a RCT to evaluate the effect of TH on reducing NSSI in adolescents with MDD and to observe its impact on psychosocial functioning. The aim is to potentially provide a new pathway for promoting the mental and physical well-being of adolescents.

Therapeutic horticulture is an adjunctive treatment method grounded in the concept of nature-based healing, with horticultural activities serving as its primary medium. According to Attention Restoration Theory (42), natural landscapes and elements allow individuals to experience themselves as part of nature, distance themselves from external pressures, and engage their minds freely without the need for directed attention, thereby facilitating emotional regulation. Nature provides rich multisensory stimulation involving sight, smell, hearing, touch, and taste, which is believed to promote physical and mental health through neural modulation and emotional responses. By guiding individuals to engage with nature, TH helps them gain a sense of self-accomplishment through collaborative and interactive gardening activities. This feature aligns well with the psychological needs of adolescents. Research suggests that some adolescents may feel uncomfortable or find it difficult to express themselves verbally during psychological interventions (43). TH offers a non-verbal, creative platform for communication, potentially reducing the perceived threat for less verbally expressive adolescents.

A strength of this study lies in its use of a non-invasive intervention. Its diverse activity design and engagement strategies are expected to enhance the appeal of the treatment and participant involvement. TH not only supplements existing intervention strategies for NSSI in adolescents with MDD but can also be implemented by trained healthcare professionals. This indicates potential for broad clinical application, particularly in resource-limited settings (19).

This study also has several limitations. First, outcomes were assessed only at baseline and immediately post-intervention. Without follow-up data, whether the effects of TH persist beyond the intervention period remains unknown. Future studies should include at least one follow-up assessment, such as 4 to 12 weeks post-intervention. Second, this single-center trial was conducted in an inpatient psychiatric ward, which, while ensuring standardized intervention delivery, limits generalizability to outpatient and community settings where most adolescents with MDD and NSSI receive care. Third, the sample was restricted to Chinese adolescents, and the findings may not extend to other populations. Fourth, the sample size is powered primarily to detect a moderate-to-large effect; smaller but potentially clinically meaningful effects may not be detected. A future multi-center pragmatic trial incorporating outpatient and community settings, a more diverse sample, and longer-term follow-up is warranted to evaluate the effectiveness of TH in real-world clinical contexts.

## Ethics and dissemination

4

The sponsor of this study is the the Affiliated Brain Hospital of Guangzhou Medical University (Address: [name]), which is responsible for the overall trial management, ethical oversight, quality assurance, and participant safety. The study protocol adheres to the principles of the Declaration of Helsinki and has been approved by the Institutional Review Board (IRB) of the Brain Hospital Affiliated with Guangzhou Medical University. Approval Number: (2025) No. (015). Any substantial amendments to the protocol will be documented with reasons, signed by relevant trial parties, and submitted to the ethics committee for approval.

During the design phase of this protocol, informal interviews were conducted with three adolescents with a history of depression and NSSI to gather their perspectives on the format and content of the proposed horticultural therapy activities. Some of their feasible suggestions were incorporated into the final intervention design. However, patients or the public were not systematically involved in the overall design or conduct of the study. As part of our commitment to transparency and respect for participants, a plain-language summary of the main findings will be offered to all participants upon completion of the trial.

The trial results, regardless of outcome (positive or negative), will be disseminated through publication in a peer-reviewed journal. The trial protocol and statistical analysis plan are presented in this article and are also available via the ClinicalTrials.gov registry (ID: NCT07115381). Upon completion of the trial, a summary of the results will be updated on the same registry. Authorship will be determined in accordance with the criteria established by the International Committee of Medical Journal Editors.
